#### Control group (placebo group)

For the control group, placebo contains 95% bitterant, edible lactose, starch, and pigment (such as lemon yellow, caramel pigment, and sunset yellow) and also includes 5% Mingjing granule to achieve the similar appearance, color, smell, taste, and weight as Mingjing granule.

#### Concomitant medications

Participants in both groups will receive 3 consecutive monthly intravitreal injections of ranibizumab (allowed to be injected at a dose of 0.5 mg per time). If necessary, they will be reinjected another during the followed up period. Decision for the reinjection will be guided on the criteria formulated by prospective OCT imaging of patients with neovascular AMD treated with intraocular ranibizumab (PrONTO) [38]: (1) a loss of 5 letters or more, (2) an increase in central retinal thickness (CRT) at least 100 μm, (3) new retinal hemorrhage appears, (4) new typical CNV, (5) fluid still exists after injection last month, and (6) any qualitative increase in the amount of fluid.

Participants will be requested not to receive any other treatments for nAMD, such as complementary treatments (e.g., herbal medicine, and acupuncture) or other medications, throughout this study. Participants will be allowed to take western medicine to treat the systematic diseases, such as hypertension or heart disease. The use of all drugs, if any, will be documented in detail in the case report form (CRF).

## Outcomes

### Primary outcome

#### The mean change of BCVA (from baseline to weeks 24 and 48)

We will assess the participants’ best-corrected distance visual acuity by ETDRS charts before and after the treatment at weeks 24 and 48. When necessary, the participants will be examined more than once.

### Secondary outcomes

#### The mean change of CRT (from baseline to weeks 24 and 48)

The participants’ eyes will be fully dilated; the examiner will take the macular fovea as the center and perform a multi-directional, 6 mm-long, radial linear scan of the most prominent macular lesions and take linear scans in the same direction after the treatment. CRT is defined as the distance between internal limiting membrane and external limiting membrane, excluding the fluid under retinal pigment epithelium (RPE). When necessary, the participants will be examined more than once.

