According to the new international consensus, AMD is defined into no obvious age-related changes, normal age-related changes, early AMD, intermediate AMD, and late AMD [3]. Late-stage AMD is further classified into two clinical forms: geographic atrophy and neovascular AMD (nAMD). nAMD is responsible for the most rapidly progressive form of AMD leading to central visual loss and will have an increasingly significant detrimental impact on quality of life among the elderly population [4, 5]. nAMD is characterized by the formation of choroidal neovascularization (CNV), the ingrowth of new blood vessels from the choriocapillaris through Bruch’s membrane into the subpigment epithelial or subretinal space [6]. Anti-VEGF agents are currently recommended as the first-line therapy for the treatment of nAMD when there is evidence of subfoveal neovascular lesions based on the notion of VEGF being a main driver of angiogenesis [7, 8]. Large multicenter randomized clinical trials have demonstrated regression of these lesions and subsequent improvement of central visual acuity in nAMD patients in a relative short term [9–12]. Although at present, the gold standard treatment for nAMD is anti-VEGF, this treatment requires repetitive intravitreal injections that carry the inherit risks of severe local adverse reactions and long term complications. Ocular inflammation, increased intraocular pressure, uveitis or less frequently endophthalmitis, retinal detachment, and retinal or vitreous hemorrhage are all serious ocular adverse events to anti-VEGF treatment [13, 14]. Others reported a lack (down to complete lack) of response with standard treatment patterns and even a decrease in treatment efficacy after repeated intravitreal injections [15].

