In China, traditional Chinese medicine has been used to treat eye diseases for thousands of years. Although there was not a specific terminology for AMD in TCM classic books of ophthalmology, there were records of such kind of diseases described as metamorphopsia. Some candidate TCM formulas for AMD have been summarized through accumulated clinical experiences. Mingjing granule, a Chinese herbal compound composed of *Astmgali Radix (huangqi), Salviae Miltiorrhizae (danshen), Lycii Fructus (gouqizi), Ecliptae Herba (mohanlian), Cattail Pollen (puhuang), Cirsii Japonici Herba Carbonisata (daji)*, is developed from an empirical formula of a famous veteran ophthalmologist of TCM. Our previous in vitro studies demonstrated that Mingjing granule could protect human retinal pigment epithelium (hRPE) cell lines from apoptosis induced by blue light, and it could also enhance the phagocytosis of RPE cells at proper concentration [20, 21]. The animal studies showed that Mingjing granule had a certain inhibitory effect on CNV proliferation and could prevent CNV leakage. The mechanism may be related with down-regulating the level of VEGF, upregulating the level of pigment epithelium-derived factor (PEDF) and decreasing M2-like macrophages in the retina of Brown Norway (BN) rat model [22–25]. In addition, some studies have reported that bone marrow-derived cells (BMCs) not only participated in the composition of CNV cells, but also secreted some cytokines to affect the occurrence and development of CNV [26–30]. In our previous study, it was shown that Mingjing granule could inhibit the contribution of BMCs in the formation of CNV [31, 32]. Furthermore, several clinical studies have reported Mingjing granule could stabilize the vision loss or improve visual acuity of nAMD, decrease the subretinal fluid, and reduce the area of CNV leakage with no significant adverse events or laboratory abnormalities [33–37]. However, to date, no high quality clinical trials have been undertaken for Mingjing granule. In this study, we will examine the efficacy and safety of the Mingjing granule in the treatment of nAMD through a randomized, double-blind, placebo-controlled trial.

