#### Retinal hemorrhage and exudation (from baseline to weeks 24 and 48)

The participants’ eyes will be fully dilated; the examiner will take the fundus photography and calculate the area of retinal hemorrhage and exudation through Image Pro Plus software. Participants’ optic disc area will be used as a record before and after the treatment at weeks 24 and 48. When necessary, the participants will be examined more than once.

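### The CRT outcome is defined to end at the external limiting membrane, so as written it omits subretinal fluid and makes its own sub-RPE exclusion redundant

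*Protocol article*

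**What the plan says.** The first secondary outcome in the protocol article is the change in CRT from baseline to weeks 24 and 48. Its operational definition is: "CRT is defined as the distance between internal limiting membrane and external limiting membrane, excluding the fluid under retinal pigment epithelium (RPE". Subretinal fluid is not mentioned there.

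Four other places bear on this definition:

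- Background, on the disease: the new vessels grow "into the subpigment epithelial or subretinal space". The article thus treats the space under the RPE and the space between retina and RPE as separate compartments.
- Background, on earlier clinical studies of the granule: the reported effects include that it could "decrease the subretinal fluid, and reduce the area of CNV leakage".
- Concomitant medications: one reinjection criterion is "an increase in central retinal thickness (CRT) at least 100" µm, with no separate definition of CRT. Another is "any qualitative increase in the amount of fluid".
- Retinal hemorrhage and exudation: the examiner takes a fundus photograph and will "calculate the area of retinal hemorrhage and exudation through Image Pro Plus software". This is an area seen from the front, not a thickness.

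**The concern.** The sentence names an outer boundary and then adds an exclusion that has no work to do at that boundary. A reader who follows the named membrane measures only the retina internal to it. A reader who follows the exclusion clause infers that everything down to the RPE counts. The two readings differ by the photoreceptor segments plus all the subretinal fluid.

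On the literal reading, the trial's only quantitative OCT outcome cannot register a fall in subretinal fluid, which the article itself reports as an effect of the product. A null CRT result could not then be taken as evidence of no effect on that fluid. If the definition were settled only after the results are known, there would be two candidate versions of one outcome and a free choice between them.

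The same undefined term also sits in the reinjection criteria. The number of injections is itself a secondary outcome, so the ambiguity may reach beyond CRT.

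**Working it through.** The documents give no figure to reproduce. The sample size rests on visual acuity, not on CRT, so no power or error-rate calculation applies. The check sets the definition against the order of the layers. That order is general anatomy and is the one input taken from outside the article.

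**Step 1. Layer order, inner to outer.** Internal limiting membrane; inner retina; outer nuclear layer; external limiting membrane; photoreceptor segments; subretinal space; RPE; sub-RPE space.

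**Step 2. Notation.** For one eye at one visit:
- A = distance from the internal to the external limiting membrane (CRT as written)
- P = thickness of the photoreceptor segments
- S = height of subretinal fluid
- D = height of sub-RPE fluid

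Thickness to the inner surface of the RPE: B = A + P + S. D enters neither A nor B.

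**Step 3. The exclusion clause.** A contains neither S nor D, so removing D from A leaves A. The clause is redundant. It becomes useful when the outer boundary is at or beyond the RPE, because it then tells the grader not to add the fluid under a lifted RPE.

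**Step 4. Change from baseline.** Change in B = change in A + change in P + change in S. With the overlying retina and the segments unchanged, a fall of X in S gives:
- CRT as written: change = 0
- thickness to the RPE: change = −X

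The documents give no fluid heights. For an assumed X anywhere from 0 to 150 µm, the two readings differ by 0 to 150 µm, that is, by X itself.

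**Step 5. What as-written CRT still measures.** Intraretinal thickening lies within A, so a change there is recorded in full.

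**Step 6. Does another outcome fill the gap?** The photographic outcome is an area. Fluid otherwise appears only in the reinjection criteria, judged as present, persisting or increased. No listed outcome measures the height or volume of subretinal fluid by OCT.

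**Step 7. The second use of the term.** Suppose subretinal fluid alone rises by 100 µm, the size named in the reinjection criterion. CRT as written rises by 0, and thickness to the RPE rises by 100 µm. Whether that criterion is met in such an eye depends on the reading. The two sections therefore need to be reconciled; this check does not say which reading is right there.

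**The case against.** The strongest reply is that this is a wording slip, not a design decision: the exclusion clause suggests the RPE was meant, and on that reading subretinal fluid is already counted. This is plausible, but the documents do not confirm it. It also does not cure the text, because anyone who follows the stated rule measures the wrong distance. Nor is this a detail left to a fuller document, since the article states the definition outright.

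Three stronger readings are tempting, and the documents do not support them.

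- *The sentence contradicts itself.* A distance ending at the external limiting membrane does exclude sub-RPE fluid. The clause agrees with the boundary and is merely redundant.
- *CRT misses a main target of the treatment.* The Background names subretinal fluid once, beside visual acuity and leakage area, and does not rank it. CRT is one of several secondary outcomes. Fluid also enters the reinjection criteria and so, indirectly, the injection count.
- *Mixed boundaries across six centres will distort the comparison.* Nothing says that centres will differ, and the quality sections call for training and common operating procedures. A constant centre offset k cancels in within-eye change: (follow-up + k) − (baseline + k) = follow-up − baseline. Only the part that varies with fluid would remain. The plan has 15 cases per group in every centre, so a centre-level shift falls on both arms, and covariance analysis is to adjust for centre and baseline. Added noise is possible; a bias between arms is not shown.

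**Conclusion.** The point stands in a limited form. As written, the CRT outcome ends internal to the subretinal space, omits subretinal fluid entirely, and carries an exclusion that removes nothing. The likeliest explanation is a mis-stated outer boundary, but that is an inference from the redundancy.

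For one eye, the loss equals the change in subretinal fluid height. Its effect on the group means or on the difference between arms cannot be given, because the documents report neither how many eyes have such fluid nor how much. The consequence is an outcome that is insensitive to one reported effect. No false positive result follows from it.

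The conclusion rests on the standard layer order and on taking the definition literally. The primary visual acuity analysis and the sample size are untouched. The correction is worth making because the definition is explicit, the outcome is the first-listed secondary one, and the remedy is cheap.

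**What to change.** Before unblinding, do one of the following for the CRT outcome:

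1. Correct the outer boundary to one that fits the exclusion clause: internal limiting membrane to RPE, with subretinal fluid included and sub-RPE fluid excluded.
2. If the external limiting membrane is truly intended, say so, drop the redundant clause, and state that CRT does not measure subretinal fluid.

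In either case, apply one segmentation at all centres and visits, and write it into the OCT operating procedure.

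The sponsor must also reconcile the term with its use under Concomitant medications, so that a reader knows which thickness each section means. No change to the reinjection rule is proposed.

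The cost is about one sentence in the protocol and one in the procedure. Stored scans can be re-measured, provided they have been kept, which the article does not state. Re-measurement repairs the outcome but not injection decisions already taken, so the reconciliation should not wait for the analysis.

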#### Retinal hemorrhage and exudation (from baseline to weeks 24 and 48)

The participants’ eyes will be fully dilated; the examiner will take the fundus photography and calculate the area of retinal hemorrhage and exudation through Image Pro Plus software. Participants’ optic disc area will be used as a record before and after the treatment at weeks 24 and 48. When necessary, the participants will be examined more than once.

#### TCM syndrome score (from baseline to weeks 24 and 48)

Evaluation of TCM syndrome refers to clinical research guidance of new investigational drug in TCM. TCM syndrome score from baseline to weeks 24 and 48 will be calculated. The scores and details of TCM syndrome are given in Table 1.

**Table 1 Tab1:** TCM syndrome score

Symptoms	Score of TCM symptom			
	None 0	Mild 1	Moderate 2	Severe 3
Dizziness and tinnitus	None	Occasionally	Sometimes, relieving after some rest	Often, still existing after some rest
Vexing heat in chest, palms, and soles	None	Vexing heat in palms and soles at night	Vexing heat in palms and soles day and night	Vexing heat in chest, palms and soles, and unwilling to cover the quilt
Soreness and weakness of waist and knees	None	Occasionally, not affecting daily life	Sometimes, weakness of legs and affecting daily life	Often, difficult to walk and affecting daily life
Dry mouth and throat	None	Slightly	Seriously	Seriously, and need some water
**Score:**				
**Tongue and pulse:**				

#### The mean number of intravitreal ranibizumab injections

We will calculate the mean number of intravitreal ranibizumab injections at week 48.

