**Methods/design:**

This is a double-blind, placebo-controlled, randomized trial of Mingjing granule as an add-on to intravitreous ranibizumab for nAMD. One hundred eighty nAMD patients from six hospitals in China will be enrolled according to the inclusion and exclusion criteria and randomly allocated into two groups, 90 in each. All participants will receive a 24-week treatment and then be followed up for another 24 weeks. The primary outcome is the mean change of best-corrected visual acuity at week 24 and 48 as compared to the baseline. The secondary outcomes include mean change in central retinal thickness, area of retinal hemorrhage and exudation, and TCM syndrome score, mean number of intravitreal ranibizumab injection, and total cost of the treatment. Indexes of safety include blood regular test, urine regular test, liver function test, renal function test, and electrocardiogram from baseline to weeks 24 and 48. Qualitative control and some standard operating processes will be formed throughout the trial. Any ocular or systemic adverse events will be treated suitably, and related data will be recorded accurately and completely in the case report form.

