## Methods

### Trial design

This is a randomized, double-blind, placebo-controlled trial. Participants will be randomly allocated into two groups, the test group and the control group. Patients in the test group will receive Mingjing granule plus ranibizumab, while those in the control group will receive placebo with ranibizumab. All of them will be followed up every 4 weeks. Mingjing granule and placebo will be dispatched every 4 weeks until week 24; ranibizumab will be administered as needed after three consecutive monthly injections until week 48 (Figs. 1 and 2). The protocol is designed following the guidelines of the Consolidated Standards of Reporting Trials and Standard Protocol Items: Recommendations for Interventional Trials (SPIRIT) (see Additional file 1 SPIRIT 2013 checklist). The trial has been registered with the Chinese Clinical Trial Registry (ChiCTR2000035990, registered on 21 August 2020).

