#### Total cost of the treatment

We will calculate the total cost of the participants’ treatment at week 48.

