#### Statistical methods

All the efficacy and safety analyses will be conducted within the full analysis set (FAS) according to the intention-to-treat principle, with all randomly assigned participants included. Last-observation-carried-forward method will be applied in the missing values. We will conduct the per-protocol set (PPS) analysis to compare the results from FAS and PPS, and safety set (SS) will be used for the safety evaluation. Data from the six centers will be combined for statistical analysis of the primary and secondary outcomes as well as adverse events. Demographic, eye examination, and laboratory characteristics will be calculated at baseline, intervention, and follow-up period. The mean ± standard deviation will be chosen for continuous variables and the comparison between the two groups will be analyzed by *t* tests with normal distribution. Non-parametric Mann-Whitney-Wilcoxon test will be used for the comparison of data with non-normal distribution. Categorical variables will be compared using *χ*^2^ statistics, while the Fisher exact test will be used when the theoretical frequency is less than 5 in more than 25% of the cells. In order to control the center and baseline effects, covariance analysis will be applied for the intergroup comparison with continuous variables and Cochran-Mantel-Haenszel test for categorical variables. All statistical tests are unilateral tests; *P* < 0.05 means statistically significant. All statistical analyses will be performed by using SPSS V.19.0.

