In summary, this protocol describes a randomized controlled trial conducted in 6 centers to evaluate the efficacy and safety of Mingjing granule in the treatment of AMD. If results of this trial demonstrates that Mingjing granule combined with ranibizumab has better efficacy, less injection times, and lower cost and good safety, it will provide useful clinically information for AMD and offer patients and ophthalmologists a new treatment option.

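### Read as written, the LOCF rule covers the week-48 injection count and treatment cost; carrying these cumulative totals forward assumes nothing accrues after drop-out and biases each arm's mean downward

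*Protocol article*

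**What the plan says.** All references are to the Protocol article.

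- **Outcomes.** The secondary outcomes include "mean number of intravitreal ranibizumab injection, and total cost of the treatment" (abstract, Methods/design). Their own sections define them as totals: "We will calculate the mean number of intravitreal ranibizumab injections at week 48" and "We will calculate the total cost of the participants’ treatment at week 48".
- **Accrual.** Under Trial design, "ranibizumab will be administered as needed after three consecutive monthly injections until week 48". Visits are every 4 weeks, so both totals can grow throughout the 48 weeks.
- **Analysis set.** Statistical methods leaves no randomised participant out: "All the efficacy and safety analyses will be conducted within the full analysis set (FAS) according to the intention-to-treat principle, with all randomly assigned participants".
- **Missing data.** The same section says: "Last-observation-carried-forward method will be applied in the missing values". No outcome is excepted and no other missing-data method is given.
- **Drop-out.** Sample size allows for 20%. Withdrawal criteria list worsening disease and use of forbidden therapy as reasons to leave.
- **Intended conclusion.** The Discussion bases the trial's message on showing that the combination "has better efficacy, less injection times, and lower cost and good safety". The abstract's Discussion also makes a reduced need for injections part of the study question.

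**The concern.** LOCF treats the last recorded value as a stand-in for the value at the end. For visual acuity this is a debatable guess that may err in either direction. For a running total the error has one direction: the total at leaving cannot exceed the total at week 48, so the carried value is either right or too low. Using it amounts to stating that the participant would have had no more injections and no more cost.

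The withdrawal criteria make this worse. Because worsening disease is a reason to leave, some leavers may be those who would have needed more treatment, yet they would be recorded as light users. Injection number and cost are two of the benefits the trial hopes to claim, so both the reported means and the comparison between arms matter.

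**Working it through.** **The plan's own figures.** The article states no expected injection count, retreatment rate or cost, so there is no figure on this point to reproduce. The related figure is the drop-out allowance. From Sample size, with a difference of 10.1 − 8.2 = 1.9 letters and SD 4:

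- (1.96 + 0.84)² × 4² × 2 / 1.9² = 69.5, or 70 per group by the normal formula. A t-based calculation gives 71, as stated.
- 71 / (1 − 0.20) = 88.75, or 89 per group, as stated.
- With 90 recruited per group, 0.20 × 90 = 18 leavers per arm are expected.

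**Inputs for the illustration**

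- From the article: three monthly loading injections, visits every 4 weeks, 20% drop-out.
- Assumed: as-needed decisions at weeks 12, 16, …, 44 (9 visits); retreatment probability p = 0.2, 0.4 or 0.6 per visit, the same for leavers and stayers; all leavers leave just before one given visit.

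**Formulas**

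- Expected 48-week count = 3 + 9p.
- Carried-forward count for a leaver = 3 + p × (as-needed visits attended).
- Shortfall per leaver = p × (as-needed visits missed).
- Understatement of the arm mean = 0.20 × shortfall.
- Spurious difference with 25% against 15% drop-out and the same p in both arms = (0.25 − 0.15) × shortfall.

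**Leaving just before week 24 (3 as-needed visits attended, 6 missed)**

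| p | Expected count | Carried-forward count | Shortfall | Arm mean too low by | Spurious difference, 25% v 15% |
|---|---|---|---|---|---|
| 0.2 | 4.8 | 3.6 | 1.2 | 0.24 | 0.12 |
| 0.4 | 6.6 | 4.2 | 2.4 | 0.48 | 0.24 |
| 0.6 | 8.4 | 4.8 | 3.6 | 0.72 | 0.36 |

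**Other timings, p = 0.2 to 0.6**

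| Leaving just before | Visits missed | Shortfall | Arm mean too low by | Spurious difference, 25% v 15% |
|---|---|---|---|---|
| Week 12 | 9 | 1.8 to 5.4 | 0.36 to 1.08 | 0.18 to 0.54 |
| Week 36 | 3 | 0.6 to 1.8 | 0.12 to 0.36 | 0.06 to 0.18 |

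**Equal drop-out in both arms.** Suppose 20% leave each arm just before week 24 and the arms truly differ by d in p. The true difference is 9d. Under LOCF it becomes 0.80 × 9d + 0.20 × 3d = 7.8d. The ratio is 7.8/9 = 0.87, so about 13% of a real difference is lost.

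**Cost.** The article gives no unit costs, so no amount can be computed. The mechanism is the same: each injection left out of the count also leaves out its cost.

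**The case against.** The strongest reply is that the article never names these two outcomes in its LOCF sentence, and that a full protocol or analysis plan, not shown, may treat resource use separately. It is true that the application is inferred. But the sentence is unrestricted, and the preceding text puts every efficacy analysis in the all-randomised set. Someone following the article would carry these totals forward, so this is a stated rule that gives a wrong result and not merely an absent detail.

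A second reply is that the planned per-protocol analysis would reveal the problem. It might, if that set excludes early leavers, but the article does not define the set. Comparing the two analyses would also not correct the total for those who left.

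Three stronger readings are tempting, and the document does not support them.

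- **A reader might infer that the rule will produce a false saving for the test arm.** That requires drop-out to differ between arms in number, timing or reason. The trial is double-blind and the article assumes a single 20% rate. With similar drop-out the effect is dilution, which works against a claim of fewer injections. More withdrawal for worsening in the control arm could likewise hide a real saving.
- **A reader might infer that leaving after loading, with three injections, earns the best score available.** It does not. Someone who leaves during loading carries forward fewer than three, and a completer who needs no as-needed injection also scores three.
- **A reader might infer that skewed counts and costs would be compared only by a rank test, so that mean differences are never estimated.** Statistical methods also provides for covariance analysis of continuous variables to control centre and baseline effects, and it reports means with standard deviations. The article gives no distribution for either outcome.

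**Conclusion.** The point holds for the rule as written. LOCF on the week-48 injection count and total cost sets everything after drop-out to zero and biases each arm's mean downward. The direction within an arm follows from the outcomes being cumulative and needs no assumption about rates. The sizes are illustrative, because retreatment rate and drop-out timing are not in the document; the week-24 case is the central illustration, and earlier or later leaving widens the range as tabulated. What happens to the comparison between arms depends on the drop-out pattern, which the document does not predict: dilution if it is balanced, a spurious advantage for the arm losing more patients if it is not.

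This should be changed before analysis, since both outcomes feed the intended conclusion. It concerns two secondary outcomes only. The sample size rests on visual acuity and does not move.

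**What to change.** 1. **Exempt both outcomes from LOCF.** State under Statistical methods that injection count and total cost are not carried forward.
2. **Keep collecting.** Where possible, record injections and costs to week 48 for participants who stop study treatment. This reduces the problem at source.
3. **Injections.** Analyse post-loading injections with a count model (negative binomial, or Poisson with robust standard errors), log post-loading follow-up time as offset, adjusted for centre. Say how participants who leave during loading, and so have no post-loading time, are handled.
4. **Cost.** Use a method that allows for censoring, such as inverse-probability weighting.
5. **Reporting.** Give between-arm mean differences with 95% confidence intervals for both outcomes, and drop-out number, timing and reason by arm.
6. **Sensitivity analysis.** The offset assumes that the rate before leaving also applies afterwards. That is doubtful when worsening disease is a withdrawal reason. Add, for example, multiple imputation of the unobserved period under a higher post-withdrawal rate.

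The cost is a few sentences in the plan, some extra programming, the effort of following those who stop treatment, and an explicit modelling assumption about the unobserved period. That assumption replaces the present implicit one of zero further use. The case report form already documents all drug use in detail (Concomitant medications); whether it captures every injection and visit date should be confirmed.
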